**Fig. 1 Fig1:**
[figure not shown]
Participant flow: T0 baseline data collection, T1 follow up assessment at 6 weeks and T2 the follow up after 12 weeks. Participants who are lost to follow-up at the T2 assessment can still be included in the analyses, due to the use of mixed models analyses

Measurements (DS-DAT and PAIC-15) will be done at baseline T0, just shortly before (T1a and T2a) and shortly after the intervention (T1b and T2b); to assess overall effects, cumulative and immediate effects (**see** Table 1). An independent research assistant performs the blinded direct observations and complies the primary outcome well-being (measured with the DS-DAT) and secondary outcome pain (measured with the PAIC-15). The nursing staff will complete the unblinding observations scales concerning the various stages of dementia at baseline T0 and they will fill in the unblinding questionnaires about QoL, NPS, agitation and symptoms of depression at T1b and T2b.

Data prescription records concerning medication use, among which psychotropic drugs, will be extracted from the electronic medical charts by [name], physician employed by the participating organization.

**Table 1 Tab1:** Instruments at different assessment moments

Outcomes/instruments	T0 week 0	T1a (pre-treatment) Week 6	T1b (post-treatment) Week 6	T2a (pre-treatment) Week 12	T2b (post-treatment) Week 12
Primary outcome					
Well-being (DS-DAT)	X	X	X	X	X
Secondary outcomes					
Pain (PAIC-15)	X	X	X	X	X
Quality of life (QUALID)	X		X		X
Neuropsychiatric symptoms (NPI-NH)	X		X		X
Agitation (CMAI)	X		X		X
Depressive symptoms (CSDD)	X		X		X
Stages of dementia (GDS)	X				
Rest/activity (Actigraphy)	X				X
Medication use (ATC classification)	X				X

DS-DAT: Discomfort Scale - Dementia of Alzheimer Type, PAIC-15: Pain Assessment in Impaired Cognition, QUALID: Quality of Life in Late-Stage Dementia Scale, NPI-NH: Neuropsychiatric Inventory Nursing Home Version, CMAI: Cohen-Mansfield Agitation Inventory, CSDD: Cornell Scale for Depression in Dementia, GDS: Global Deterioration scale, ATC: Anatomical Therapeutic Classification system

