### Sample size

The sample size calculation is based on the study’s primary outcome measure, the Discomfort Scale – Dementia of Alzheimer type (DS-DAT) [51] for F-tests ANOVA repeated measures. To determine the sample size required to assess relevant effects, we used data from the Cochrane review on music-based therapeutic interventions [27]; the effect size for emotional well-being and quality of life (SMD 0.32, 95%CI 0.02 to 0.62). The correlation between multiple assessments of the DS-DAT was calculated with the data of Schalkwijk et al. [57] as 0.6. Using a type I error of 0.05, a power of 0.80, two follow-up measurements and 2 groups, a sample size of 30 in each group is required, totaling 60 participants to achieve 0.81 power. According to the availability of music therapists we estimated that the study would take approximately 3 years. The mortality rate in the nursing home setting is high. Moore [58] stated that the length of stay in long-term care facilities in Europe countries is almost 2 years. It is estimated that about a one third (20 of 60 residents) may die or will be lost to follow up for other reasons during the study period, so we need to enroll a total of around 70 till 80 residents for this study.

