#### Data analysis

Immediate effects are defined as the difference in change between outcomes 15 min before and after the intervention sessions. Cumulative effects are effects over time not including those immediately after the session (i.e., built-up effect over time and measured before the session in order not to include possible immediate effects of the session). Overall effects are effects over time including those immediately after the session. Immediate, cumulative and overall effects are analyzed with mixed model analysis to consider the dependency of the repeated observations within the patient.

For the immediate effects, the outcome will be the post-test (T1b, T2b) and adjustment will be made for the pre-test (T1a, T2a). For the cumulative effect, the outcome will be the pre-test and an adjustment will be made for the baseline. For overall effects, the outcome will be post-test and adjustment will be made for the baseline.

For all treatment effects, effects at the different time-points will be analyzed by adding a time x treatment interaction to the mixed model analysis. Furthermore, both crude and adjusted (adjustments for gender, age, cognitive deterioration and for medication use, which will be added as a time-dependent covariate) will be performed. In the mixed-model analysis, we will also evaluate whether an adjustment for the correlated observations within facilities is necessary. There is no need to impute missing data because mixed models can handle missing assessments.

In explorative post-hoc analysis we will evaluate whether the intervention effects will be different for patients with a musical background by adding the interaction between the intervention variable and presence of musical background.

Sleep quality data of the MotionWatch (CamNtech Ltd, Cambridge, UK) will be analyzed with Motionware software version 1.2.1. Five parameters will be calculated: Interdaily stability, Intradaily variability, Relative Amplitude, most active period of 10 h and least active period of five hours. The 5 parameters will be analyzed with linear regression analyses with the values measured after the intervention period as outcome with an adjustment for the baseline vale of particular outcome.

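### The immediate-effect model adjusts for a week 6 or 12 pre-session score that treatment may already have changed, so it does not estimate the within-session difference in change that the plan defines

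*Protocol article*

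**What the plan says.** The Data analysis section of the protocol article separates three effects: immediate, cumulative and overall.

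- Immediate, as defined: "Immediate effects are defined as the difference in change between outcomes 15 min before and after the intervention sessions".
- Immediate, as modelled: "For the immediate effects, the outcome will be the post-test (T1b, T2b) and adjustment will be made for the pre-test (T1a, T2a").
- Cumulative, as defined: "built-up effect over time and measured before the session in order not to include possible immediate effects of the session".
- Cumulative, as modelled: "For the cumulative effect, the outcome will be the pre-test and an adjustment will be made for the baseline".
- Overall: the post-session score, adjusted for baseline.

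The Participants timeline section fixes the timing: "Measurements (DS-DAT and PAIC-15) will be done at baseline T0, just shortly before (T1a and T2a) and shortly after the intervention (T1b and T2b"). Table 1 places T1a and T1b at week 6 and T2a and T2b at week 12. T0 is therefore the only score taken before treatment. It is the adjuster for the cumulative and overall effects but is not named for the immediate effect.

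**The concern.** Adjusting a post score for a pre score is sound when the pre score precedes randomised treatment, because the arms then have the same expected pre score. T1a and T2a do not meet that condition. The plan makes the same scores the outcome of its cumulative analysis, so it tests whether treatment changes a variable and also uses that variable as a covariate.

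If the arms do differ before the session, the adjusted coefficient compares residents who happen to have equal week 6 or week 12 scores. Randomisation does not protect that comparison, and it is not the difference in change that the plan sets out to estimate. Part of a lasting benefit would be reported a second time as a session effect. Telling the two apart, for the primary outcome (DS-DAT) and for pain (PAIC-15), is why scores are taken on both sides of the session, and the Discussion presents short-term and long-term estimation as a strength of the design.

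**Working it through.** **The plan's own figure.** The article gives no figure for the immediate-effect model. Its only related figures are in the Sample size section: "the effect size for emotional well-being and quality of life (SMD 0.32, 95%CI 0.02 to 0.62"), a DS-DAT correlation "as 0.6. Using a type I error of 0.05, a power of 0.80, two follow-up measurements and 2 groups", and "a sample size of 30 in each group is required, totaling 60 participants to achieve 0.81 power". For the between-groups test in repeated-measures ANOVA, the noncentrality is f²·N·m / (1 + (m - 1)ρ). With f = 0.32, N = 60, m = 3 and ρ = 0.6 it is 0.1024 × 60 × 3 / 2.2 = 8.38 on (1, 58) degrees of freedom, and the power is 0.812. The stated 0.81 is reproduced, with 0.32 entered as Cohen's f and three measurements counted. Whether that entry is right is a separate matter. Here 0.32 and 0.6 serve only as illustrative inputs.

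**Inputs and assumptions.**
- c, the cumulative effect on the pre-session score: 0.32 SD, borrowed from the planning effect size. The documents give no value for c itself.
- r, the correlation between scores before and after one session: not given. The plan's 0.6 is for repeated DS-DAT assessments in general. Scores minutes apart may correlate more strongly, so 0.6 to 0.9 is shown.
- True within-session difference: zero, so the post-session group difference equals the pre-session one.

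**Algebra for one visit.** Let d_pre and d_post be the group differences before and after the session, and b the within-group slope of post on pre.

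- Defined immediate effect: d_post - d_pre.
- Planned coefficient: d_post - b·d_pre = (d_post - d_pre) + (1 - b)·d_pre.

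The second term vanishes only if d_pre = 0 or b = 1. Lower DS-DAT means less discomfort, so d_pre = d_post = -0.32:

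- b = 0.6: -0.32 + 0.6 × 0.32 = -0.128 SD
- b = 0.8: -0.32 + 0.8 × 0.32 = -0.064 SD
- b = 0.9: -0.32 + 0.9 × 0.32 = -0.032 SD

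The difference in change is 0 in all three.

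**Check with the planned model.** A random-intercept REML model was fitted to both visits, with all other correlations at 0.6. The coefficient comes from 200,000 simulated residents. The rejection rates of a nominal 5% test come from 2,000 trials at each size. The true difference in change is 0 throughout.

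| c (SD) | r | Fitted slope | Planned coefficient (SD) | Rejects, N = 60 | Rejects, N = 80 |
|---|---|---|---|---|---|
| 0 | 0.6 | 0.547 | -0.001 | 4.9% | 4.2% |
| 0.32 | 0.6 | 0.544 | -0.150 | 13.4% | 16.2% |
| 0.32 | 0.7 | 0.676 | -0.103 | 11.6% | 13.4% |
| 0.32 | 0.8 | 0.791 | -0.067 | 8.1% | 8.0% |
| 0.32 | 0.9 | 0.899 | -0.031 | 5.8% | 6.2% |

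The coefficients follow the algebra. At r = 0.6 the fitted slope is 0.544, and (1 - 0.544) × 0.32 = 0.146. The mixed-model slope lies somewhat below r, so the single-visit figure of 0.128 is slightly low for the planned model.

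With the within-session change as outcome, the coefficient was 0.00 SD to two decimals and rejection was 3.4 to 5.4% in every scenario.

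**Adding T0 to the planned model makes it worse.** At c = 0.32 and r = 0.6 the coefficient becomes -0.219, with rejection of 26.5% (N = 60) and 35.6% (N = 80). T0 takes over part of the prediction, so the slope on the pre-session score falls. For one visit with all correlations at 0.6 that slope is 0.6 / 1.6 = 0.375, and (1 - 0.375) × 0.32 = 0.20.

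**The case against.** The best case for the plan has four parts.

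1. *The error is conditional.* With no cumulative effect the planned model is unbiased for the difference in change, and with an adverse cumulative effect the error would count against music therapy. This stands, and it limits the claim to what the model can do. But the plan expects and tests a cumulative effect, so the analysis should not depend on its absence.

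2. *The inputs are borrowed.* The 0.32 comes from a review of emotional well-being and quality of life, and the example assigns all of it to the cumulative part. The 0.6 is not a correlation around one session. This also stands, which is why a range is given. At 0.9 the discrepancy is about 0.03 SD and rejection is close to nominal.

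3. *The conditional question is defensible.* DS-DAT has a floor at 0, so a group already lowered before the session has less room to fall. If part of the pre-session difference fades during the session, the difference in change is itself non-zero. With d_post = 0.6 × d_pre it is -0.192 + 0.32 = +0.128 SD, against music therapy, while the planned coefficient is near zero. That is a fair argument for a different estimand. The article does not make it: its definition is a difference in change, and nothing in it says that a conditional comparison was intended.

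4. *The defined quantity can be recovered.* The overall effect minus the cumulative effect, both adjusted for T0, estimates the difference in change, and neither uses T1a or T2a as a covariate. This is true for the point estimate. It supplies no direct test or interval, and the result reported as the immediate effect would still be the one from the mismatched model.

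**Conclusion.** The concern holds. The stated model does not estimate the stated immediate effect whenever treatment has shifted the pre-session score and the slope of post on pre is below 1. Nothing elsewhere in the article repairs this. It is a stated modelling choice, not a detail left to a later analysis plan.

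If the cumulative effect is 0.32 SD and nothing differs within the session, the planned mixed model reports about 0.15 SD at a pre/post correlation of 0.6, falling to about 0.03 SD at 0.9. A nominal 5% test then rejects in roughly 6 to 16% of trials of 60 to 80 residents. Both inputs are assumptions, and the size scales with the cumulative effect. The direction favours music therapy when that effect is beneficial. The cumulative and overall analyses are not affected.

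**What to change.** For the immediate effect, use the within-session change (T1b - T1a and T2b - T2a) as the outcome of the mixed model, with the T0 score of the same scale (DS-DAT or PAIC-15) as baseline covariate. Drop T1a and T2a as covariates. An equivalent route is to model pre- and post-session scores jointly, with T0 as covariate and a treatment-by-session-phase term, and to read the immediate effect from that term. Do not simply add T0 to the present model.

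If a comparison at equal pre-session scores is also wanted, define it as a separate, secondary quantity and say that randomisation does not protect it.

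The change is one of wording in the analysis plan and uses only data already to be collected. The price is a somewhat larger standard error. The single-visit formula compares a variance of 2(1 - r) for the change score with 1 - r² for the adjusted model. At r = 0.6 that is 0.80 against 0.64, a standard-error ratio of √1.25 = 1.12; at r = 0.8 it is 0.40 against 0.36, a ratio of 1.05. In simulations of the two-visit mixed model the increase was smaller, about 1 to 3%.

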Consequently, the question arises if adequate strategies are available for treating this triad of symptoms, i.e. NPS, pain, and sleep disturbances, and hence, improving QoL, in people with dementia. NPS are often treated pharmacologically with psychotropic drugs, which frequently cause unwanted side effects, such as somnolence and extrapyramidal symptoms [16]. Psychosocial interventions, however, may obviate the indication for antipsychotic drug prescriptions [17]. Moreover, therapies such as validation, reminiscence, psychomotor therapy, multisensory stimulation and music therapy can increase QoL of people with dementia and their caregivers [18]. Sikkes et al. reviewed the evidence and found that various non-pharmacologic treatments such as music therapy effectively improve behavior [19].

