### Secondary outcomes measures

Secondary outcomes are also assessed in all /participating residents and include pain, quality of life, neuropsychiatric symptoms (agitation, anxiety, symptoms of depression), quality of sleep and psychotropic drug use.

**Pain** will be assessed by a blinded research assistant at baseline, six weeks and twelve weeks during 2 min before and after the intervention session or individual attention with the PAIC-15 (Pain Assessment in Impaired Cognition) [54, 55] which is an observational assessment instrument that lists 15 items and uses scores from 0 to 3 for each item. PAIC-15 comprises three domains: facial expression, body movements and verbalizations/vocalizations. Each domain has 5 items and the total score is the sum of all items, ranging from 0 to 45. The research assistant will be trained in using the PAIC-15.

**Quality of life** will be rated by non-blinded nurses at baseline (T0), at six weeks (T1) and at twelve weeks (T2) with the Quality of Life in Late-Stage Dementia Scale (QUALID) [56] that can be used with late-stage dementia patients in institutional settings and has been designed for proxy-rating by nurses. Responses reflect patient behavior over the past seven days. The QUALID consists of eleven items that are short and simple and is characterized by a good reliability and validity and the Dutch translation was a valid measure for quality of life in patients with advanced dementia [57]. The total score is the sum of all items, ranging from 11 to 55. Lower scores indicate a higher quality of life.

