**Physical activity**: rest-activity data will be collected by a MotionWatch (CamNtech Ltd, Cambridge, UK). The MotionWatch measures the arm movements of the participant; based on these movements, the rest-activity and physical activity are determined. It quantifies accelerations due to motor activity of the arm and integrates these over I-minute periods. The MotionWatch has the size and shape of a watch, is worn on the dominant wrist. The participants will be asked to wear the MotionWatch twenty-four hours a day for 1 week in the week before the intervention starts (T0) and the week directly after the last intervention session (T2). Nurses are asked to temporarily take off the MotionWatch when the participant takes a shower, performs another activity in which the MotionWatch could be exposed to too much water. Nurses will report the time that devices are taken off. Five parameters are calculated: Interdaily Stability (IS), Intradaily Variability (IV), Relative Amplitude (RA), most active period of 10 h and least active period of five hours. First, the IS variable that quantifies the strength of coupling between the rest-activity rhythm and supposedly stable Zeitgebers (e.g., meals) is calculated. IV, which quantifies the fragmentation of the rhythm, that is, the frequency and extent of transitions between rest and activity. RA quantifies the difference between the main activity (day) and rest (night) periods. The parameter of 10 most active hours (M10) is used to determine the amount of physical activity. The parameter (L5) are least active periods of five hours to determine rest activity.

Data on chronic psychotropic drug use will be derived from the electronic medical chart. Psychotropic drugs will be categorized into antipsychotics, anxiolytics, hypnotics, antidepressants and anti-dementia drugs according to the Anatomical Therapeutic Classification (ATC) system.

Any attrition or adverse effects of the interventions will be documented. The interventions will be discontinued if, in consultation with the physician or psychologists, harmful effects are observed and are expected to continue with exposure to any of the two interventions.

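### The adjusted models condition on post-randomisation medication use, itself a secondary outcome, and no week-6 value of it is scheduled

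*Protocol article*

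**What the plan says.** The Data analysis section plans crude and adjusted mixed models for the immediate, cumulative and overall effects. The adjusted version has "adjustments for gender, age, cognitive deterioration and for medication use, which will be added as a time-dependent covariate". For all treatment effects, "effects at the different time-points will be analyzed by adding a time x treatment interaction to the mixed model analysis". On missing data it says "There is no need to impute missing data because mixed models can handle missing assessments".

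Three other places bear on the medication covariate:

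- **Secondary outcomes measures** ends its list of outcomes with "quality of sleep and psychotropic drug use", and gives the source: "Data on chronic psychotropic drug use will be derived from the electronic medical chart".
- **Table 1**, in the row "Medication use (ATC classification"), has marks at T0 and T2b only. The T1a, T1b and T2a cells are empty. DS-DAT and PAIC-15 are marked at all five moments, and the nurse-rated scales at T0, T1b and T2b.
- **Background and rationale** states: "Psychosocial interventions, however, may obviate the indication for antipsychotic drug prescriptions".

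The Fig. 1 caption adds that residents without a T2 assessment still contribute, because mixed models are used.

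**The concern.** There are two separate problems.

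**Conditioning on a variable that treatment may affect.** Medication use at follow-up is measured after randomisation. The protocol treats psychotropic use as something the intervention might alter, both by listing it as an outcome and through its own rationale. Holding such a variable fixed removes any part of the effect that runs through prescribing. It can also open a path through unmeasured severity that drives both prescribing and discomfort. The adjusted coefficient then answers a different question from the effect of being assigned to music therapy.

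**No scheduled value at week 6.** A mixed model fitted by likelihood tolerates missing outcomes. It does not tolerate a missing covariate: that row is dropped. The no-imputation sentence covers the first case but not the second. If no week-6 medication value is obtained, the adjusted model loses T1, and with it the promised time-specific effects. Crude and adjusted results would then differ in participants, time-points and estimand at once, and a difference between them could not be attributed to covariate balance.

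**Working it through.** **Inputs.** From the Sample size section: correlation between DS-DAT assessments 0.6, two follow-ups, 30 per group, SMD 0.32. From Table 1: the medication schedule above. Two readings are assumed: the medication covariate is the Table 1 medication row, and the week-12 chart value serves both T2a and T2b.

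**The plan's own figure.** The plan gives no figure for the adjusted model. Its power of 0.81 at N = 60 is reproduced by a between-groups repeated-measures F-test with f = 0.32, three measurements and exchangeable correlation 0.6: noncentrality = 0.32² × 60 × 3 / (1 + 2 × 0.6) = 8.38, power 0.812. This enters the SMD as Cohen's f, which is a separate matter. Here it only supports using 0.6 as an exchangeable correlation.

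**Step 1: rows at risk.** With 60 completers there are 120 follow-up rows per model, 60 at T1 and 60 at T2. Without a week-6 medication value and without imputation, the 60 T1 rows drop. One time-point remains, so a time x treatment term cannot be estimated. Residents seen at T1 but lost before T2 drop out entirely, contrary to the Fig. 1 caption. Their number is not given. Taking 80 enrolled and 20 lost, it lies between 0 and 20.

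**Step 2: precision if T1 is lost.** For the baseline-adjusted mean of k follow-ups with exchangeable correlation ρ, the variance factor is (1 + (k − 1)ρ)/k − ρ².

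- k = 2: (1 + 0.6)/2 − 0.36 = 0.44
- k = 1: 1 − 0.36 = 0.64
- Ratio 0.64/0.44 = 1.45; effective sample 0.44/0.64 = 69%

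Power at 30 per group, by Φ(d/√(2v/30) − 1.96), falls from 0.46 to 0.34 at d = 0.32, and from 0.96 to 0.87 at d = 0.64 (the difference that f = 0.32 corresponds to).

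These figures hold for the effect averaged over both follow-ups, adjusted for T0, without dropout. They do not describe the immediate-effect model, where "the outcome will be the post-test (T1b, T2b) and adjustment will be made for the pre-test (T1a, T2a"), nor the T2-specific effect, which rests mainly on T2 rows in any case.

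**Step 3: direction of the distortion.** If medication has effect b on discomfort and treatment changes the proportion medicated by Δp, the coefficient with medication held fixed is total − b × Δp, absent unmeasured common causes. The documents give neither b nor Δp, so the values below are assumptions. The outcome is scaled so that its SD apart from the drug effect is 1, the total effect is fixed at −0.32, and each scenario simulates 1,000,000 residents.

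| Medicated, control vs music therapy | Drug effect on discomfort | Unmeasured severity | Adjusted estimate |
|---|---|---|---|
| 50% vs 50% | −0.5 | no | −0.32 |
| 50% vs 35% | −0.3 | no | −0.37 |
| 50% vs 35% | +0.3 | no | −0.27 |
| 50% vs 21% | −0.3 | no | −0.41 |
| 50% vs 36% | 0 | yes | −0.27 |
| 50% vs 36% | −0.3 | yes | −0.31 |
| 50% vs 24% | 0 | yes | −0.22 |

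Check of row 2: −0.32 − (−0.3)(0.345 − 0.498) = −0.366. Where treatment leaves prescribing unchanged there is no bias. Otherwise the estimate moves either way.

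**The case against.** The strongest reply is that the crude models are also planned. They contain no medication term, keep every T1 row, support the time x treatment interaction and estimate the effect of assignment. That stands, and it limits the point to the adjusted models. The article does not say which set is primary, but an article may leave that to the full protocol or SAP, so it is not counted here.

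Second, medication is read from charts, not assessed at the bedside, so week-6 prescriptions could be extracted later. This also stands. A reader might infer from Table 1 that T1 data are certain to be lost; the documents show only that no week-6 extraction is scheduled. Extraction would repair the missing rows but not the conditioning. Carrying the T0 value to T1 would mean the covariate is not time-dependent there.

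Third, a reader might infer that the adjusted estimate is necessarily biased towards no effect. The documents do not support that. The rationale says only that prescribing may change and speaks of antipsychotics, while the comparison is with individual attention over 12 weeks and the record is of chronic use. The change may be small, and Step 3 shows no fixed direction.

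Fourth, because T2a is blank too, a strictly literal reading would leave the cumulative-effect model with no rows at all. That presses the table too hard: T2a and T2b bracket one session, and one chart reading at week 12 can serve both.

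Finally, asking whether an effect persists given concurrent medication is a legitimate supplementary question, provided it is labelled as such.

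**Conclusion.** The point holds for the adjusted models only. As specified, they condition on a post-randomisation variable that is a secondary outcome and that the protocol says psychosocial interventions may change. They therefore cannot safely be read as the effect of assignment. The size and sign of any distortion cannot be determined from the documents, and it is nil if treatment leaves prescribing unchanged.

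Separately, Table 1 and the Data analysis section do not fit together. Unless week-6 prescriptions are extracted, T1 drops from the adjusted models, the adjusted interaction is lost and the Fig. 1 caption no longer holds for them. The cost for the follow-up-averaged, baseline-adjusted effect would be about 45% more variance, under exchangeable correlation 0.6 and no dropout.

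This should be fixed before analysis. It does not invalidate the trial's planned analysis as a whole, because the crude models are untouched.

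**What to change.** In the adjusted models, replace time-dependent medication use with psychotropic use at T0, alongside gender, age and baseline GDS. Analyse post-baseline psychotropic use as the secondary outcome it is. This changes a line or two and needs no new data, since T0 medication is already collected. It keeps both follow-ups in the adjusted models.

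If a model with time-dependent medication is still wanted, label it exploratory, state that it does not estimate the effect of assignment, and reconcile Table 1 with the Data analysis section by adding a week-6 chart extraction. The cost is one further chart reading per resident.

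In either case, limit the no-imputation sentence to missing outcomes.
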